## Abstract

**Background:**

Gynecologic cancer has a high frequency of anemia, which is associated with increased morbidity and mortality. Blood transfusion is used to correct anemia, but carries its own side effects and problems in the blood supply have been emerging. As such, methods other than transfusion are needed to correct anemia in patients with cancer.

**Primary Objective:**

To determine whether intravenous administration of high-dose iron supplements before and after surgery as a patient blood management program is helpful in correcting anemia and reducing the frequency of transfusion in patients with gynecologic cancer.

**Study Hypothesis:**

Patient blood management will reduce the transfusion rate by up to 25%.

**Trial Design:**

This prospective, multicenter, interventional, randomized controlled study will consist of three steps. In step 1, the safety and effectiveness of patient blood management for surgical patients before, during, and after surgery will be evaluated. In steps 2 and 3, the safety and effectiveness of patient blood management in patients before, during, and after adjuvant radiation therapy and chemotherapy will be evaluated.

**Major Inclusion/Exclusion Criteria:**

Patients who are diagnosed with gynecologic cancer (ie, endometrial cancer, cervical cancer, ovarian cancer) and scheduled for surgery will be included and their iron deficiency status will be assessed. Only those with a pre-operative hemoglobin level of 7 g/dL or higher will be included. Patients who underwent neoadjuvant chemotherapy or pre-operative radiation therapy will be excluded. Also, patients with serum ferritin >800 ng/mL or transferrin saturation >50% on serum iron panel tests will be excluded.

**Primary Endpoint:**

Rate of transfusion within 3 weeks after surgery.

**Sample Size:**

Eligible participants will be randomly assigned in a 1:1 ratio (167 patients each) into the patient blood management group and the conventional management group.

**Estimated Dates for Completing Accrual and Presenting Results:**

Patient recruitment will be completed by mid-2025, and management and follow-up will be completed by the end of 2025.

**Trial Registration Number:**

NCT05669872.

## Introduction

Anemia is prevalent in cancer patients and affects 20–80% of patients with solid tumors.^1^ The causes of anemia in cancer patients include tumor-specific factors and treatment-related factors. Cancer-related chronic inflammation and cytokines can contribute to anemia by mediating the inhibition of erythropoietin production and iron sequestration.^2^ Acute bleeding from surgery, kidney failure due to chemotherapy, and bone marrow dysfunction due to chemotherapy and radiation or other treatments also contribute to cancer-related anemia.^3^ Most cases of anemia in cancer patients are iron deficiency anemia or anemia with functional iron deficiency.^4^ Anemia in cancer patients is associated with increased morbidity and mortality.^5 6^ Symptoms of anemia, which often manifest as shortness of breath, lethargy, palpitations, and fainting, can interfere with daily functioning and contribute to low quality of life.

Gynecologic cancer is associated with a high frequency of anemia (~85%). The frequency of anemia and blood transfusion is also reported to be very high during surgery, chemotherapy, and radiation therapy, which are the mainstay of treatment for gynecologic cancers.^7^ While the frequency of anemia before surgery ranges from 26% to 36%, the pre-operative and post-operative transfusion rates range from 41% to 77%.^8^ Previous studies have reported that anemia is associated with poorer outcomes for treatment and survival in gynecological cancers.^5 6^ Anemia is also associated with local tumor control failure, potentially related to treatment resistance by tumor hypoxia; accordingly, the hemoglobin level before treatment is a well-known prognostic factor of gynecologic malignancies.^5^ Therefore, the importance of anemia correction before treatment is increasingly emphasized in gynecologic oncology.

Blood transfusion was considered the only way to quickly correct anemia in the presence of acute blood loss; however, transfusion itself also carries side effects including transfusion-associated graft versus host disease, transfusion-transmitted diseases, alloimmunization to blood cell antigens, transfusion-related lung injury with pulmonary decompensation, and immunomodulation.^9^ Recently, problems in the supply of blood products for transfusion have emerged due to low birth rates, aging populations, and decrease in blood donations due to COVID-19.^10^ Therefore, the concept of patient blood management to replace blood transfusion and its necessity is being increasingly recognized. Patient blood management is defined as a patient-centered systematic evidence-based approach to improving patient outcomes by managing and preserving the patient’s own blood while promoting patient safety and empowerment.^11^ Patient blood management usually consists of three stages for patients undergoing surgery. Before surgery (stage 1), anemia is diagnosed and treated, and the red blood cell mass is maximized by improving the production of blood cells and supplying high-dose intravenous iron. During surgery (stage 2), hemostasis is optimized and blood loss is reduced through medical and surgical methods. After surgery (stage 3), the physiological reserve is optimized to prevent anemia. Through these stages, patient blood management can reduce the need for blood transfusions, cut associated healthcare costs, and stockpile blood components for those who need them the most.^12^

In a recent randomized controlled trial in adults with isovolumic anemia following radical gastrectomy, the use of intravenous ferric carboxy-maltose compared with placebo was more likely to result in an improved hemoglobin response at 12 weeks and led to significantly greater improvements in iron panels such as serum ferritin level and transferrin saturation levels.^13^ This method involving ferric carboxy-maltose can be applied to radiation therapy or chemotherapy for patients with cancer. However, there are no prospective studies that have evaluated the safety and efficacy of patient blood management for patients with gynecologic cancer undergoing surgery. Therefore, the aim of this study is to determine whether intravenous administration of high-dose iron supplements before and after surgery as a patient blood management program is helpful in correcting anemia and reducing the frequency of blood transfusion in patients with gynecologic cancer undergoing surgery. We also plan to determine whether the use of high-dose iron supplementation during adjuvant radiation (with or without chemotherapy) or adjuvant chemotherapy is helpful in the correction of anemia.

## Methods and Analysis

### Trial Design

This is a prospective, multicenter, interventional, comparative, randomized controlled trial involving a total of 15 institutions in South Korea, of which the Asan Medical Center (Seoul, South Korea) will serve as the leading institution. This study was approved by the institutional review board of Asan Medical Center (approval ID: 2022–1674, approval date December 6, 2022) and is registered in ClinicalTrial.gov (identifier number: NCT05669872). Informed consent will be obtained from all patients before participation.

The study schema is shown in Figure 1. This study consists of three steps. In step 1, the safety and effectiveness of patient blood management for surgical patients before, during, and after surgery will be evaluated. In step 2, the safety and efficacy of patient blood management of patients before, during, and after adjuvant radiation therapy or concurrent chemoradiation therapy after surgery will be evaluated. In step 3, the safety and efficacy of patient blood management for patients before, during, and after adjuvant chemotherapy after surgery will be evaluated. Study treatments in each step are as follows.

**Figure 1 F1:**
[figure not shown]
Study schema. (CC)RT, (concurrent chemo-) radiation therapy; KGSO, Korean Society of Gynecologic Oncology; PBM, patient blood management.

#### Step 1: Anemia Correction in Surgery

Blood tests will be performed between 2 and 6 weeks before surgery and anemia will be corrected according to the test results for each group as follows. The treatment and examination schedule for step 1 is shown in Figure 2.

**Figure 2 F2:**
[figure not shown]
Examination and treatment of anemia in step 1 (surgery). Hb, hemoglobin; PBM, patient blood management; preop, preoperative; postop, postoperative; POD, postoperative day; wks, weeks.

##### Patient Blood Management Group

If the hemoglobin level is between 7 g/dL and 12 g/dL in the preoperative blood test, 1000 mg of ferric carboxy-maltose will be administered between 2 and 6 weeks before surgery. During surgery, the need for transfusion will be decided according to the judgment of the attending surgeon and anesthesiologist in case of hemodynamic instability. A blood test will be performed the day after surgery, and if the hemoglobin level is between 7 g/dL and 12 g/dL, 1000 mg of ferric carboxy-maltose will be administered; if the hemoglobin level is 7 g/dL or less, two packs of red blood cells (RBC) will be transfused. The hemoglobin level will be re-evaluated at 3 weeks post-operatively.

##### Conventional Management Group

If the hemoglobin level is between 8 g/dL and 10 g/dL, one pack of RBC will be transfused and, if the hemoglobin level is 8 g/dL or less, two packs of RBC will be transfused. Erythropoietin and oral iron supplements will be allowed, but not intravenous iron supplements. During surgery, the need for transfusion will be decided according to the judgment of the operating surgeon and anesthesiologist in case of hemodynamic instability. A blood test will be performed the day after surgery, and if the hemoglobin level is between 8 g/dL and 10 g/dL, one pack of RBC will be transfused; if the hemoglobin level is 8 g/dL or less, two packs of RBC will be transfused. Post-operatively, erythropoietin and oral iron supplements will be allowed. The hemoglobin level will be re-evaluated 3 weeks post-operatively.

Surgical treatment and adjuvant treatment will be carried out according to the guidelines published by the Korean Society of Gynecological Oncology, which are consistent with the recent guidelines of the National Comprehensive Cancer Network. All surgery-related complications occurring during and after surgery during hospitalization will be evaluated using Dindo’s classification.^14^

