### Endpoints

The primary endpoint is the rate of transfusion within 3 weeks after surgery. The secondary endpoints include transfusion rate within 3 weeks after radiation and chemotherapy, and the comparison of hemoglobin levels, frequency of anemia and blood transfusion before adjuvant therapy, frequency of delayed adjuvant therapy due to anemia, cost-effectiveness, quality of life, and adverse events after iron supplement treatment or blood transfusion.

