### Sample Size

We performed sample size calculation through the Z-test with unpooled variance. Previous studies showed that the expected transfusion rate without patient blood management is 40%,^15 16^ and that the blood transfusion rate could be reduced by 25% through patient blood management. The following assumptions were made for calculating the required number of study participants: transfusion rate before, during, and after surgery when implementing patient blood management of 40%; level of significance α=0.05 (two-sided); and type II error, β=0.2 (ie, power=80%). The sample size was calculated using PASS version 15 (NCSS, Kaysville, Utah, USA) using the above settings and a total of 150 patients per group (total of 300 patients) were deemed necessary. Considering a dropout rate of 10%, we intend to enroll 167 patients per group (total 334 patients).

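### The objective describes the program only as intravenous iron, but the arms also differ in transfusion rules (10 vs 7 g/dL), so the primary transfusion result cannot be attributed to iron alone

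*Protocol article*

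**What the plan says.** All references are to the protocol article.

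- **Endpoint** (Endpoints): "The primary endpoint is the rate of transfusion within 3 weeks after surgery".
- **Post-operative rule, controls** (Step 1, Conventional Management Group): hemoglobin is tested "the day after surgery, and if the hemoglobin level is between 8 g/dL and 10 g/dL, one pack of RBC will be transfused". At 8 g/dL or less, two packs are given. The effective trigger is 10 g/dL.
- **Post-operative rule, PBM** (Step 1, Patient Blood Management Group): "if the hemoglobin level is 7 g/dL or less, two packs of red blood cells (RBC) will be transfused". Between 7 and 12 g/dL the prescribed action is 1000 mg of ferric carboxymaltose. The effective trigger is 7 g/dL.
- **Pre-operative rule**: controls at 8 to 10 g/dL are also transfused before surgery ("one pack of RBC will be transfused and, if the hemoglobin level is 8 g/dL or less", two packs). The PBM group gets iron at 7 to 12 g/dL and has no pre-operative transfusion rule.
- **During surgery**, PBM group: "During surgery, the need for transfusion will be decided according to the judgment of the attending surgeon and anesthesiologist", in case of hemodynamic instability. The control text is equivalent.
- **Objective** (Abstract, Primary Objective): whether intravenous "high-dose iron supplements before and after surgery as a patient blood management program is helpful in correcting anemia and reducing the frequency of transfusion". The aim in the Introduction repeats this: "determine whether intravenous administration of high-dose iron supplements before and after surgery as a patient blood management program is helpful". Neither mentions a transfusion threshold.
- **Other framing**: the Study Hypothesis, the main purpose in Statistical Methods and the intended conclusion in the Discussion speak of PBM as a whole.

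**The concern.** A patient whose day-1 hemoglobin lies above 7 and up to 10 g/dL has a prescribed primary-endpoint event in the conventional group and prescribed iron in the PBM group. Iron given on day 1 cannot change the day-1 value that drives this decision, so that part of the contrast comes from the rule. Pre-operative iron may still raise day-1 hemoglobin, so iron can contribute, but the primary comparison mixes the two.

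The objective and the aim ask whether intravenous iron, as the program, reduces transfusion. The comparison answers whether iron together with a more restrictive transfusion rule does. The Introduction's general account of PBM covers anemia treatment with intravenous iron, limiting blood loss and optimizing physiological reserve. It does not list a lower trigger, so the reader is not told that the trigger is part of what is tested. The Discussion hopes to inform treatment guidelines, where iron could be credited with a reduction that came wholly or partly from the trigger.

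The gap concerns the transfusion half of the objective. The anemia half has hemoglobin among its secondary endpoints.

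**Working it through.** **1. The plan's own figure.** Sample Size gives: "expected transfusion rate without patient blood management is 40" percent, a reduction by 25%, two-sided alpha 0.05, 80% power, unpooled Z-test. Reading the reduction as 40% to 25%:

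n = (1.96 + 0.8416)² × (0.40×0.60 + 0.25×0.75) / 0.15² = 149.1, so 150 per group; 150/0.90 = 166.7, so 167.

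Both stated figures reproduce, so the planned effect is 15 points.

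**2. What the rules prescribe.**

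| Time and hemoglobin (g/dL) | Conventional | PBM |
|---|---|---|
| Before surgery, 7 to 10 | transfuse | iron |
| During surgery | clinical judgment | clinical judgment |
| Day 1, 7 or less | transfuse | transfuse |
| Day 1, above 7 up to 10 | transfuse | iron |
| Day 1, above 10 up to 12 | no transfusion rule | iron |

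**3. What the day-1 trigger alone could produce.** The document gives neither the spread of hemoglobin nor the share transfused during surgery, so these are assumptions:

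- control rate 40% (Sample Size);
- identical normal day-1 hemoglobin in both arms, i.e. no iron effect, with SD 1.2, 1.5 or 2.0 g/dL;
- full adherence to the rules and no transfusion after day 1;
- intra-operative transfusion counted in the rate, with the same share d in both arms.

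Formulas:

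- q = P(day-1 hemoglobin ≤ 10) = (0.40 − d)/(1 − d)
- mean = 10 − SD × z(q)
- p7 = Φ((7 − mean)/SD)
- PBM rate = d + (1 − d) × [p7 + c × (q − p7)]

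Here c is the share of PBM patients between 7 and 10 g/dL who are transfused on clinical grounds anyway.

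Example with d = 0.25, SD = 1.5, c = 0: q = 0.15/0.75 = 0.20; mean = 10 + 1.5×0.8416 = 11.26; p7 = Φ(−2.84) = 0.0022; PBM rate = 0.25 + 0.75×0.0022 = 0.252. The difference is 14.8 points.

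Trigger-only difference in percentage points (range over the three SDs), with the chance of a significant unpooled Z-test at 150 per group in parentheses:

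| Intra-operative share d | c = 0 | c = 0.30 | c = 0.50 |
|---|---|---|---|
| 25% | 14.3–15.0 (76–80%) | 10.0–10.5 (45–48%) | 7.1–7.5 |
| 30% | 9.6–10.0 (42–45%) | 6.7–7.0 (23–24%) | 4.8–5.0 |
| 35% | 4.9–5.0 (14–15%) | 3.4–3.5 (9–10%) | 2.4–2.5 |
| 38% | 2.0 (6–7%) | 1.4 (6%) | 1.0 |

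At d = 40% the difference is 0. Shares below 25% would give larger differences. They are not relied on, because with full adherence they imply a PBM rate below the planned 25% before iron does anything.

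**4. Sensitivity.** With 80% control adherence (q divided by 0.8, control rate held at 40%) and c = 0, the differences are 13.9–14.9, 9.5–10.0, 4.8–5.0 and 2.0 points at the four shares. With intra-operative transfusion correlated 0.3 to 0.5 with low day-1 hemoglobin (simulation), they are 14.3–15.0, 9.6–10.0, 4.9–5.0 and 1.9–2.0. The intra-operative share and c drive the result; the SD hardly matters.

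**The case against.** The strongest reply is that this is a strategy trial. Different transfusion rules by arm are deliberate and openly stated, and the hypothesis, arm names, statistical purpose and intended conclusion all speak of PBM. Even the objective and aim add that iron is given as such a program, and nowhere does the text say that the result will be credited to iron alone. All of this stands. It limits the point to how the objective and aim are worded, but does not remove it: those two statements give iron as the program's only content.

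The magnitude can also be attacked. It depends on an assumed intra-operative share, normality, adherence and no later transfusion within a 3-week window, and it counts intra-operative transfusion in an endpoint worded as after surgery. This also stands, so no single size is claimed. The attribution problem follows from the rules themselves and needs none of the scenarios.

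Three stronger readings are tempting, and the document does not support them:

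- *The comparison is invalid or its result an artefact.* Randomization protects the comparison of the two strategies, and pre-operative iron may have a real effect.
- *PBM patients between 7 and 10 g/dL cannot be transfused.* The text prescribes iron there but does not forbid a clinically indicated transfusion, hence the columns with c above 0.
- *Iron and trigger cannot be separated at all.* Day-1 hemoglobin is measured in both arms, and hemoglobin is a secondary endpoint. These allow a partial separation, although they are not free of the rules.

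**Conclusion.** The point holds as a limit on attribution. The trial validly compares two strategies, but the primary objective and aim name only one ingredient of the PBM strategy. Because the prescribed transfusion rules differ (day 1: 10 against 7 g/dL; before surgery: a rule for controls only), a difference in the primary endpoint can arise without an iron effect and cannot be credited to iron alone.

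How much of a positive result the trigger would supply cannot be determined from the document. Under the stated assumptions it ranges from almost none to about the planned 15 points, depending mainly on the share transfused during surgery and on how often PBM patients between 7 and 10 g/dL are transfused anyway. The pre-operative rule is not in the calculation, because transfusions before surgery may fall outside the endpoint as worded. It should be fixed because the primary question is described too narrowly; nothing in the conduct of the trial has to change.

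**What to change.** 1. In the Primary Objective and in the Introduction's aim, state the objective as the effect of the whole strategy. For example: *whether PBM, consisting of high-dose intravenous iron before and after surgery plus a restrictive transfusion rule (7 g/dL), compared with conventional management (transfusion at 10 g/dL or less before and after surgery, no intravenous iron, erythropoietin and oral iron allowed), helps correct anemia and reduces transfusion.* Add that the primary result will not be attributed to iron alone.
2. Unless the full protocol or analysis plan already has it, add a supportive by-arm table from data already collected: the proportion with day-1 hemoglobin, before any post-operative transfusion, at or below 7, 8 and 10 g/dL, shown with intra-operative and pre-operative transfusion. Label it less trigger-dependent, not trigger-neutral: controls may be transfused before surgery by rule, and intra-operative decisions are unblinded judgment. The absence of this table from a condensed article is not itself a fault.

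The cost is wording in two places, one small table and a narrower claim about iron. Care, primary endpoint and sample size stay as they are.

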### Statistical Methods

The main purpose of this study is to compare the transfusion rate according to the implementation of patient blood management in patients with gynecologic cancer undergoing surgery. For other safety endpoints such as laboratory tests and vital signs, continuous data will be presented using descriptive statistics (ie, mean, SD, median, min, max) for each group, and categorical variables will be presented using frequency and percentage. If necessary, the Student t-test or Wilcoxon rank sum test will be performed for continuous data to test for differences in other safety endpoints between groups, and the χ^2^ test or Fisher’s exact test will be performed for categorical variables. Statistical analysis will be performed using IBM SPSS Statistics for Windows, Version 26.0 (IBM Corp, Armonk, New York, USA).

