## Discussion

Anemia in patients with cancer is associated with increased morbidity and mortality. Traditionally, blood transfusion has been performed to correct anemia in these patients, but transfusion has its own side effects and problems in blood supply have emerged recently. Therefore, many studies have been conducted to evaluate whether anemia can be effectively corrected using methods other than blood transfusion. In a phase III randomized study conducted at seven centers in South Korea, a placebo or ferric carboxy-maltose was administered to patients who had undergone extensive gastrectomy and had a hemoglobin of <7–10 g/dL after a few days of surgery.^13^ The hemoglobin levels were compared at 12 weeks after surgery and the results showed that the hemoglobin level was significantly higher in the iron supplement group by 2 g/dL or more.

However, there are no prospective studies that have evaluated the safety and efficacy of patient blood management for patients with gynecologic cancer undergoing surgery. Therefore, this trial is designed to demonstrate the safety and effectiveness of patient blood management in patients with gynecologic cancer undergoing surgery, adjuvant (chemo-)radiation therapy, and chemotherapy. In addition, there are no randomized controlled trials that have evaluated whether patient blood management can reduce the transfusion rate and improve surgical outcomes. This study will be the first randomized controlled trial to evaluate these issues. Through this study, we seek to provide evidence that patient blood management can effectively lower the transfusion rate of patients with gynecologic cancer. Since anemia and blood transfusion are associated with a poor survival prognosis in patients, developing a strategy to reduce transfusion during treatment would lead to improvements in the quality of treatment and increase the survival rate.^5^ In addition, the reduction in blood transfusion and transfusion complications can bring about economic effects through the reduction of medical costs and hospitalization. A reasonable and economical medical system can be established by enabling efficient pre- and post-surgery management. Furthermore, our results may pave the way to standardize blood management guidelines for patients with gynecologic cancer before, during, and after surgery and adjuvant treatment, and develop them as treatment guidelines.

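### Graded surgical complications stop at discharge and the adverse-event endpoint is worded as events after iron or transfusion, so these secondary safety comparisons can differ by arm without a true effect

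*Protocol article*

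**What the plan says.** Two separate safety items are defined in the protocol article.

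- **Surgical complications.** The last paragraph of Step 1 states: "All surgery-related complications occurring during and after surgery during hospitalization will be evaluated using" a severity classification. It sits under the Conventional Management Group heading, but it reads as covering all surgical patients. No closing day is given other than the end of the hospital stay.
- **Adverse events.** The Endpoints section lists, among the secondary endpoints, "adverse events after iron supplement treatment or blood transfusion". This item carries no discharge limit.

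The Statistical Methods section adds a third group: "For other safety endpoints such as laboratory tests and vital signs, continuous data will be presented using descriptive statistics". Neither restriction applies to it, and between-group tests are to be done if necessary.

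The triggers for treatment differ by arm. In the PBM group, at a pre-operative hemoglobin of 7 to 12 g/dL, "1000 mg of ferric carboxy-maltose will be administered between 2 and 6 weeks before surgery". In the conventional group the rule begins "If the hemoglobin level is between 8 g/dL and 10 g/dL, one pack of RBC will be transfused and" goes on to two packs at 8 g/dL or less. In that group, "Erythropoietin and oral iron supplements will be allowed, but not intravenous iron supplements".

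By contrast, "The primary endpoint is the rate of transfusion within 3 weeks after surgery", and both arms have a hemoglobin check at 3 weeks. The trial is open label, and evaluating safety is a stated aim of step 1 (Trial Design).

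**The concern.** A randomised comparison is protected when every patient is observed over the same period by a rule that does not depend on what happens after allocation. Neither clinical-event rule meets that standard. Discharge is a post-randomisation decision taken by staff who know the allocation, and receipt of iron or blood is largely determined by the assigned strategy.

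The arm discharged earlier would have less time in which a graded complication could be recorded. The arm with the wider treatment trigger would have more patients in whom an event could qualify, and in PBM patients treated pre-operatively the count would begin weeks before surgery. What is at stake is the interpretation of the secondary safety comparisons.

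**Working it through.** **1. The plan's own figure.** The article gives no safety figure. Its sample size is reproduced here only to fix the group size used below. With 40% versus 25%, two-sided 5%, 80% power and unpooled variance:

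n = (1.960 + 0.842)² × [0.40×0.60 + 0.25×0.75] / (0.40 − 0.25)² = 7.849 × 0.4275 / 0.0225 = 149.1, so 150 per group; 150 / 0.90 = 166.7, so 167. Both match the Sample Size section.

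**2. Mandated exposure in step 1, arms side by side** (from the two group descriptions):

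| Hemoglobin, g/dL | PBM | Conventional |
|---|---|---|
| above 12 | none | none |
| 10 to 12 | intravenous iron | none (oral iron and erythropoietin allowed) |
| 8 to 10 | intravenous iron | one pack of red cells |
| 7 to 8 | intravenous iron | two packs |
| 7 or less, day after surgery | two packs | two packs |

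The 10 to 12 band is where an event can follow mandated treatment in one arm and not in the other.

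**3. Window ending at discharge (illustration).** Assumed: the same constant daily hazard in both arms, 21-day risk R = 30%, stays of 5 to 10 days. Daily hazard = −ln(0.70)/21 = 0.01698. Recorded risk over a stay of L days = 1 − exp(−0.01698 × L).

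- L = 5: 8.1%. L = 7: 11.2%. L = 10: 15.6%.
- 5 versus 7 days: ratio 0.73. 5 versus 10 days: ratio 0.52. Equal stays: ratio 1.00.

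The chance of a significant result against the longer-stay arm at 150 per arm is Φ[(|p₁ − p₂| − 1.96·SE₀)/SE₁]. Here SE₀ = √[2p̄(1 − p̄)/150] and SE₁ = √{[p₁(1 − p₁) + p₂(1 − p₂)]/150}. With no bias it is 2.5% per direction.

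- 5 versus 7 days: 14% (11% to 19% for R from 20% to 40%).
- 5 versus 10 days: 52% (36% to 66%).

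Swapping the stays reverses the direction.

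**4. Counting only after exposure (illustration).** Assumed: the same 20% event risk in every patient, counted only in those exposed. Counted per randomised patient = 0.20 × share exposed.

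| Exposed, PBM vs conventional | Counted | Ratio | Chance of significance in that direction (event risk 10% to 30%) |
|---|---|---|---|
| 40% vs 40% | 8% vs 8% | 1.0 | 2.5% |
| 60% vs 40% | 12% vs 8% | 1.5 | 21% (12% to 31%) |
| 80% vs 40% | 16% vs 8% | 2.0 | 57% (31% to 78%) |
| 30% vs 50% | 6% vs 10% | 0.6 | 25% (14% to 36%) |

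The wider PBM trigger points towards the second and third rows. The last row needs more exposure in the conventional arm, which is possible if oral iron counts.

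**5. The denominator matters too (illustration).** Assumed hemoglobin mix: 35% above 12, 35% at 10 to 12, 22% at 8 to 10, 8% at 8 or less. Assumed risks: 10%, 15%, 25% and 35%, the same in both arms. The risk over all patients is 0.035 + 0.0525 + 0.055 + 0.028 = 17.1% in each arm.

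- Exposed patients as denominator: PBM 0.1355/0.65 = 20.8%; conventional 0.083/0.30 = 27.7%.
- All randomised as denominator, exposed events only: 13.6% versus 8.3%.

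The same patients favour PBM on the first count and conventional management on the second. With all events in all randomised patients, the two arms agree.

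**The case against.** A reader might infer that all safety is captured only in hospital and only after iron or blood. The documents do not support that. The two limits apply to two different items, and laboratory tests and vital signs carry neither.

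A reader might also infer that PBM will shorten the stay and so look safer. The hospital-stay rule is identical in both arms, and length of stay is not an endpoint. The only support is a Discussion sentence hoping for "reduction of medical costs and hospitalization" as an economic effect, with no figure for the surgical admission. That makes unequal stays conceivable, not established.

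Nor does it follow that post-discharge harm under the lower PBM transfusion trigger goes unrecorded. Those patients receive iron or blood after surgery and so fall within the adverse-event endpoint, which does not stop at discharge. Only the complication grading does.

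It would also be too strong to say that every untransfused conventional patient above 10 g/dL drops out of the adverse-event count. Oral iron is allowed, and the article does not say whether it counts as iron supplement treatment. The article gives no denominator either, and it does not say that unexposed patients go unobserved.

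A loss of complications proportional to the shorter stay (1 − 5/7 = 29%) would be an overstatement. Complications during surgery are counted whatever the stay, and early clustering would shrink the effect further.

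Finally, graded complications are not named in the Endpoints section, and the full protocol may define collection periods and denominators. Their absence from an article is no finding.

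All of this narrows the point. What remains is stated text: a window closed by discharge, and an endpoint worded by exposure where the arms have different triggers.

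**Conclusion.** The point holds in narrow form. Both rules depend on post-randomisation events in an open-label trial, and the discharge-bounded window is not aligned with the fixed 3-week primary window. If length of stay or the share exposed differs by arm, a difference can appear with no true effect. If neither differs, the mechanisms illustrated in steps 3 and 4 give no bias.

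The size cannot be derived from the article. Under the assumed inputs the ratios run from about 0.5 to 2.0. They show what is possible and do not predict a result or its direction. The consequence is confined to secondary safety comparisons; the primary endpoint and the 150 (167) per group stand. This is a cheap improvement, not a threat to the trial's main conclusion.

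**What to change.** - Record graded surgical complications from surgery to the existing 3-week post-operative visit in all randomised patients, regardless of discharge date.
- For step 1, record adverse events from randomisation to the same visit in all randomised patients, whether or not they receive iron or blood. Collection in steps 2 and 3 is not cut short by this.
- Compare both by randomised arm, with all randomised patients as the denominator.
- Keep in-hospital complications and reactions after iron or transfusion as descriptive subsets, and state whether oral iron counts as iron supplement treatment.

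With one common window and equal true risk, the expected ratio returns to 1.00 and the false-positive rate to 5%. The cost is a change to the endpoint wording and the case report form, and slightly more event recording. It needs no new visit, no change in treatment and no additional patients.
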